#### Secondary outcome measures

##### Fugl-Meyer Upper Extremity test (FM-UE)

The motor deficit of the UL will be assessed using the FM-UE [27]. The FM-UE score allows to differentiate proximal UL movements (shoulder, elbow, and forearm; score 44) and distal UL movements (wrist and hand; score 24) totalling 66 points. The results of the scoring system of the FM-UE enable the classification of the patient as having mild (≥ 40/66), moderate (between 21/66 and 39/66) or severe (≤ 20/66) UL impairment. The FM-UE has excellent reliability, validity, and sensitivity to change and it is regarded as the gold standard to assess UL impairment [30]. The estimated clinically important difference of the FM-UE scores ranges from 4.25 to 7.25 points [57].

##### Box and Block Test (BBT)

The global hand grasping capacity will be assessed using the BBT [52]. The BBT requires the patient to move as many 2.5 cm^3^ cubes in 60 s (with only one cube been displaced at the time) from a box compartment to another separated by a 15.2-cm-tall partition using the paretic hand and then with the non-paretic hand. Only one trial is given. The patient score is equal to the number of these cubes transported in 60 s. For healthy subjects, the score at the BBT is between 75 and 80 cubes displaced in a minute. For our population, the smallest real difference before and after intervention is of five or six cubes [14].

##### Barthel Index (BI)

The activities of daily living will be assessed with the Barthel Index (BI [51]). BI assesses the patient’s level of independence to perform ten basic life activities: eating, bathing, personal care, ability to dress themselves, motility, urinary regularity, bathroom use, chair-bed transfer and inversely, mobility, and climbing stairs. The score generated varies from zero (totally dependent) to a maximum score of 100 (totally independent).

##### Actimetry assessment of paretic UL use in ADL

The actual use of the paretic UL in ADL in their own house environment will be assessed continuously over a 7-day period (prior to V1; after V2; after V3) with two wrist worn actimetry bracelets (AX3, Newcastle Helix, UK) on the paretic and non-paretic UL [3]. The two actimetry bracelets record 3D acceleration (± 8 G, 50 Hz) to get objective measures of the actual functional use of the paretic UL in the activities of daily living. The different measures will be the UseRatio (functional use ratio between the two UL), the Use (number of functional movements by the paretic UL), the intensity of paretic UL movements, and the actimetry profile of the different activities using the paretic UL [3, 44, 46, 58].

##### Proximal Arm Non-Use (PANU) score

The non-use of the paretic UL will be quantitatively assessed by the Proximal Arm Non-Use (PANU) score (0–100% [4, 5]) during a seated arm reaching task using kinematic measurements (see “Functional motor tasks” section for details). The PANU score quantifies the shoulder-elbow joint non-use that a patient can voluntarily cancel [5] and has good reliability and repeatability [4]. The PANU score of 6.5% is the limit beyond which we can consider the patient having proximal arm non-use [5].

In the seated arm reaching task (see Fig. 5a), patients will be comfortably seated on a chair with armrests. A target is located in front of them (centred in relation to the body) at a distance such that the base of the metacarpal of the index finger touches the target when the elbow is extended, the shoulder at ~ 30° of flexion and the back resting on the chair. Patients will have to reach the target in two conditions: (i) spontaneous condition, where patients are free to use trunk flexion compensation as they spontaneously do, and (ii) maximal condition, where patients limit trunk movements with the help of a light tactile feedback from the therapist to minimize trunk movements. A practice trial will be done to familiarize the patients on the timing of reaching (~ 5 reaches/20 s based on pilot testing) by following a recorded voice of investigator to start and return phase of the reaching movement. After a 2-min rest period, the patients will be required to repeat the reaching movements first with the paretic UL then with the non-paretic UL over 3 trials (20 s with 20 s rest between trials). The spontaneous condition will be undertaken first followed by the maximal condition. Kinect V2 (Microsoft, USA) and LSL-Kinect software (see “Availability of data and materials” for details) will be used to stream and analyse the UL kinematics to calculate PANU score and other kinematic variables according the methods outlined in our previous work [4].

**Fig. 5 Fig5:**
[figure not shown]
Functional motor tasks. Seated reaching task with the patient at rest and UL extended to reach towards the target (**a**). Circular steering task with the patient viewing the circle tunnel on the screen and moving the mouse cursor with the hand within the boundaries of the circle tunnel (**b**). During these UL motor tasks cortical motor region activation (fNIRS and EEG) and kinematics (hand, arm, and trunk) are simultaneously recorded using Lab Streaming layer technology (see “Availability of data and materials” section for more details)

#### Other/exploratory outcome measures

##### Functional motor tasks

The experimental setup for the Seated Reaching and Circular Steering tasks will allow synchronous measurements of motor cortical region activation (functional near infrared spectroscopy-fNIRS and electroencephalography-EEG) and UL kinematics using lab streaming layers (LSL, https://github.com/labstreaminglayer/App-LabRecorder).

In the circular steering task (see Fig. 5b), a computerized version of a circular steering task (LSL-Mouse; see “Availability of data and materials” for details) based on the speed–accuracy trade-off [8] will be used to determine performance improvements of the paretic UL. Patients will be comfortably seated in front of a table with a graphical tablet (A3 size, Wacom, Kazo, Japan) and stylus moulded onto a mouse pad for ease of hand placement for stroke patients. A 24-in. display screen placed behind the tablet will show the circular tunnel and a cursor matching the location of the stylus on the tablet. The patient’s hand will be placed at a location of the tablet corresponding to the top of the circle tunnel allowing comfortable elbow extension without trunk flexion from the chair. The instruction to the patient will be to move the cursor within the circular tunnel for 20 s, as fast as possible and some errors hitting the tunnel walls are allowed. Biasing speed over accuracy of movements is emphasized in the circular steering task to allow maximum potential of patients to gain benefit from andodal tDCS of the ipsilesional motor cortex [8, 31]. A practice trial will be provided to the patient where they will be able to see their errors online and movement path such that the investigator will inform the patient to speed up the movement if errors are less than 15% (based on pilot testing). After a 2-min rest period, the circular steering task will be repeated over 3 trials (20-s task interspaced by 20-s rest) first with the paretic UL followed by the non-paretic UL.

In the index of performance (IP), speed and accuracy will be calculated as in our previous work [8]. Additionally, trunk displacements will be recorded using the LSL-Kinect and trunk compensation will be determined.

In the Armeo Ladybug game (see Fig. 4), the Ladybug game on the Armeo exoskeleton will allow changes UL movement performance and motor cortical region activation to be determined from a task that will be used during the 3-week combined VRT and anodal HD-tDCS program. The ladybug task will require the patient to “catch” a series of 48 Ladybugs appearing one after the other at different positions on the display screen in less than 3 min. The UL kinematics will be recorded by the Armeo software, which will be analysed to determine the variability trajectory of the end effector to reach the target. Performance metric of the speed and smoothness of UL movements will be based on our previous work [64].

##### Motor Cortical region activation (fNIRS/EEG)

Ipsilesional and contralesional motor cortical region activation will be measured during the 3 functional motor tasks (Seated reaching task, Circular steering task, and Armeo ladybug game) using a Starstim fNIRS integration (Starstim8, Neuroelectrics, Barcelona, Spain; Octamon+, Artinis Medical Systems, the Netherlands) that allows combined EEG and fNIRS measurements with the same neoprene cap used for the HD-tDCS setup. The 8 EEG electrodes and 8 fNIRS channels will be configured above the left and right motor cortical region (around C3 and C4 electrode locations, respectively on a 10–20 system; see Fig. 6).

**Fig. 6 Fig6:**
[figure not shown]
Locations of the electroencephalography (EEG) electrodes and functional near-infrared spectroscopy (fNIRS) probes over the bihemispheric motor cortical regions. The Starstim fNIRS integration (Starstim8-Octamon+) allowed for 8 EEG (4 electrodes [black circles] on the left [C3, FC5, FC1, CP1] and right [C4, FC2, FC6, and CP2] hemispheres) electrodes and 8 fNIRS (4 fNIRS transmitters (red circles) located ~ 3 cm from a receiver (numbered 1, 2) on each hemisphere) channels

EEG measures functional brain activity by detecting the variations of electrical fields created by neuronal activation, while fNIRS allows indirect measurement of neuronal activity by monitoring local changes in the oxygenated (O_2_Hb) and deoxygenated (HHb) haemoglobin concentrations in the cerebral microcirculation based on neurovascular coupling mechanism [2, 59]. These two imaging methods have previously been independently used to evaluate changes in motor cortical region activation during functional movements following stroke rehabilitation programs [7, 18], and fNIRS has already been tested and validated during various UL tasks by our team (reaching task in [6]; force task in [18] and in [20]).

In fNIRS analysis, changes in the average, peak, and area under the curve values of the concentration of O_2_Hb and HHb in the ipsilesional and contralesional motor cortical region will be determined during the 3 functional UL movement tasks. In addition, a laterality index (LI) will be calculated for each task and trial [20] to determine whether sensorimotor cortex activation, based on O_2_Hb concentration, during the task is mainly contralesional or ipsilesional. The LI will be calculated from the ratio of ipsilesional and contralesional O_2_Hb concentration, which varies between − 1 (purely contralesional activation) and + 1 (purely ipsilesional activation [18]).

In EEG analysis, changes in sensorimotor cortex neural oscillations will be measured by the magnitude and ratio of alpha- and beta-frequency power in both ipsilesional and contralesional motor cortical regional at rest and during the 3 functional UL movement tasks. The event-related desynchronization (ERD) of the alpha-motor mu rhythm (8–12 Hz) and of the low beta rhythm (12–20 Hz) will be calculated at the start of each trial. These specific band frequencies are well known to be involved during UL movement for healthy subjects but also for stroke patients [7].

##### Pain and fatigue of the paretic upper limb

Before and after each VRT session, pain and fatigue of the paretic UL during movement will be collected using a visual analogue scale (VAS). The VAS consists of a straight line measuring 10 cm, with 0 cm corresponding to the absence of pain/fatigue and 10 cm corresponding to maximum pain/fatigue.

##### Perceived exertion

Perceived difficulty will be evaluated after each VRT session using the Borg scale of perceived exertion [12]. The Borg scale extends from 6 “no feeling of exertion,” to “very, very hard,” which rates a 20.

### Data management and monitoring

During the trial, the sponsor of the project, Montpellier University Hospital (contact: Director of Innovation and Research Department) will be responsible of monitoring the study.

#### Collecting and data management

The participant will only be identified by a unique identification number, the first letter of the name, the first letter of the first name, his gender, and the year of birth. An identification list of subjects will be kept in the investigator’s file. The investigator will ensure that the anonymity of each person participating in the study is guaranteed. Information will be collected for each participant in a standardized observation booklet filled out by the investigator or the co-investigator.

The source documents are the original documents, data, and files, from which the data concerning the research participants are entered in the electronic case report form (eCRF) by dedicated employees at Montpellier University Hospital. The investigator undertakes to authorize direct access to the source data of the study during control, audit, or inspection visits. Data from the actimetry, from the Armeo and from the functional motor tasks (kinematics, performance, EEG/fNIRS) will be extracted from the local password-protected computers and stored on the EuroMov centre private server that can be accessed only by the registered investigators (KB, CM, DM, MM, SP, PJ, GD) with reinforced authentication during the duration of the project. All data will be checked monthly by the PI to ensure that all protocols and ethical guidelines for data collection and analysis are followed.

Study data are entered through the e-CRF developed using ENNOV CLINICAL software, which allows real-time data quality control. In order to meet regulatory requirements, this software complies with the recommendations concerning computerized systems for the management of clinical trials and electronic signature and standards. Connection is made by a unique password and identifier specific to each user, which will only give him access to his patients’ data. An audit function is integrated into the software, allowing traceability of the data collected as well as the modifications made. The encrypted data will then be transmitted to the department responsible for data management via a secure internet connection. The eCRF must consist of all the information required by the protocol.

The individual data necessary for the analysis of the study will be:
Entered into e-CRFs as they are obtained, whether they are clinical or para-clinical dataAnonymized by the investigator (the participant will be identified only by a unique identification number, the first letter of the name, the first letter of the first name, and the year of birth; an identification list of subjects will be kept in the investigator’s file)Authenticated by an electronic signature of the investigatorAll entered; therefore, the missing data must be justified

First, the data entered in the e-CRF is checked and validated by the Clinical Research Associate (CRA) from the source documents. Secondly, the data manager performs additional computerized consistency tests based on the presence of non-standard, missing, aberrant, or inconsistent data and which are performed regularly during patient recruitment and follow-up. All consistency tests are defined in advance in specifications proposed by the data manager and validated by the investigator, the statistician, and the CRA. Each inconsistency identified on the eCRF (“Queries”) is the subject of a request for correction or justification from the investigator (response to “Queries”). The latter undertakes to make himself available to the members of the research team and to provide them with all the additional information required to resolve these errors. This information is reported in the study database. Once the study is complete, namely the data required for the protocol and any additional data entered (self-questionnaires), the data monitored and validated, the study database is frozen.

The maintenance of the database is the responsibility of the Clinical and Epidemiology Research Unit of the Innovation and Research Department of the study sponsor. The data is kept in an ASCII type format.

The data encoding is integrated into eCRFs. The computer files and the follow-up of any modification are saved and made available by the Innovation and Research Department of Montpellier University Hospital. The database freezing is carried out according to the Innovation and Research Department procedures. The freeze is documented by a database freeze certificate. It takes place once all the data is verified and the corrections requested from the investigators are obtained.

The closure of the trial including the closure of the centres will be carried out in accordance with Good Clinical Practice and International Conference on Harmonization. The medical, administrative, and observation records (all study-related documents) will be kept for the duration of the study, then archived in locked filing cabinets at the PRM department of Montpellier University Hospital, for a minimum period of 15 years after the end of the project.

#### Monitoring and quality control

The project will be monitored by the CRA. Appropriate monitoring will be implemented based on a risk grid related to the project. In accordance with this grid, the CRA will carry out regular follow-ups of the project’s investigation centres (establishment visit, follow-up according to the rhythm of inclusions and a closing visit). All checks will be the subject of a monitoring report by written report (traceability of visits). The investigators agreed to comply with the requirements of the sponsor and the competent authority with regard to an audit or inspection of the research. The audit might be applied to all stages of research, from the development of the protocol to the publication of results and the classification of data used or produced in the context of the research.

### Adverse events management

Any adverse events (i.e., muscle or joint pain, syncope, falls and injuries) or serious adverse events (SAEs, i.e., any incident requiring hospitalization) during the HD-tDCS/VRT sessions or testing protocol will be reported to an investigator by filling out the Incident Report Form (IRF). All adverse events will be also recorded, treated, and evaluated upon signing of the consent and until the end of the patient’s participation in the study and/or the end of the collection of adverse events. The Innovation and Research Department will (1) assess the causal link between the serious adverse event and the research; (2) assess whether the adverse reaction is expected or unexpected, using the reference document, the protocol in force for this study; and (3) declare all serious and unexpected adverse reactions within the regulatory deadlines to the competent Health Authorities and the Ethics Committees concerned and informs the investigators at intervals appropriate to the research. Given the type of research (interventional research involving category 2 humans), no annual safety report is planned for this study and given the low risks added by the study, an independent oversight committee will not be established for this study.

### Statistical analysis

#### Sample size

Allman et al. [1] reported that compared to sham, real anodal tDCS (1 mA, conventional montage, ipsilesional motor cortex) combined with 9 days of UL rehabilitation in chronic stroke patients had a moderate effect size *d* = 0.4 on the WMFT at 3 months after the intervention. In the meta-analysis of Chhatbar et al. [16], UL motor recovery (FM-UE) in a chronic stroke population was superior in the group receiving a real tDCS (in comparison to sham) with higher current density and smaller electrode size (large effect size *g* = 1.23). Because we will use anodal HD-tDCS with a higher current density (2 mA) and longer rehabilitation dose (13 days) in chronic stroke patients, we estimate that our protocol should have an effect size of *d* = 0.8 on the WMFT at 3 months. Using an alpha bilateral risk of 5% and a power of 80%, 26 patients per group are needed for analysis. If we count a loss of 10% of the patients, we will have to recruit 58 patients (*n* = 29 per group).

#### Statistical method

Statistical analysis will be performed using the latest version of the free R software. A *p*-value of 0.05 will be considered significant for all analyses. All outcome measures will be assessed at V1, V2, and V3. The primary outcome will be the difference between both groups (*intervention, placebo*) at V3 on the WMFT. The secondary outcomes will be the changes between V1 and V2 (learning) and between V2 and V3 (retention) for both groups.

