#### Secondary outcome measures analysis

The secondary outcome measures (FM-UE, BBT, PANU, BI, and actimetry) will be used to assess the changes in UL impairment, function, non-use, and ADL from V1 at inclusion to V2, and V2 to V3.

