With support from our primary and secondary outcome results, the impact of the ReArm project for the public health care system could be a better efficiency of paretic UL rehabilitation for chronic stroke patients at unchanged or lower cost. With combined HD-tDCS and VRT, we expect a better paretic UL recovery without an increased rehabilitation time commitment, without an increased human resource costs (e.g., physiotherapy and occupational therapy time) but with a relatively minor hardware related costs (tDCS device and consumables) costs. Moreover, this innovative treatment with HD-tDCS is adapted to a majority of patients, since tDCS allows to stimulate the patient while receiving rehabilitation treatment. Therefore, tDCS has a promising clinical potential in post-stroke rehabilitation [61, 63]. Thus, improving the efficiency of recovery for a majority of stroke patients may have an impact on patients’ health and on public health costs.

The benefit for the patients taking part of this study could be a better efficiency of the rehabilitation without changing the length of the rehabilitation programs. Indeed, the association of the two methods proposed (anodal HD-tDCS and VRT) could allow, for the same dose of rehabilitation, a better and faster recovery of the paretic UL function. Patients could thus enter in the virtual spiral of “use it and improve it” aided by the rehabilitation efficiency [38]. This could lead the patient to a better independence on daily life activities and to a better life quality.

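### The 0.05 significance rule covers every analysis, so the secondary and exploratory labels place no limit on how a small p-value may be declared

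*Protocol article*

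**What the plan says.** The Statistical method section applies one criterion throughout: a p-value of "0.05 will be considered significant for all analyses". The same section names the primary comparison ("The primary outcome will be the difference between both groups" at V3 on the WMFT) and defines the secondary outcomes as changes over two periods, V1 to V2 and V2 to V3.

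The Secondary outcome measures analysis section lists five outcomes ("FM-UE, BBT, PANU, BI, and actimetry) will be used to assess the changes"). The Actimetry section divides one of them into four: "The different measures will be the UseRatio", the amount of use, the intensity and the activity profile. The Other/exploratory outcome measures analysis section adds performance, fNIRS and EEG measures from three motor tasks. It plans tests of the group-by-time interaction overall and for each of the two periods.

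The sample size rests on the primary outcome alone. The Discussion opens its public-health argument "With support from our primary and secondary outcome results".

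**The concern.** A protocol may leave the handling of multiplicity to the analysis plan. Here the protocol makes a decision instead: it gives every analysis the same threshold and the same word for crossing it. Ranking outcomes as primary, secondary and exploratory normally tells the reader how much weight a small p-value can bear. Under this rule the ranking has no such consequence.

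The trial is powered for a large effect (d = 0.8) on one outcome. If that comparison is null, the rule would still allow an isolated secondary or exploratory p-value below 0.05 to be reported as significant without qualification. What is at stake is over-reading of non-primary results.

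**Working it through.** **The plan's own figure.** The protocol states "Using an alpha bilateral risk of 5% and a power of 80%, 26 patients per group are needed for analysis", for d = 0.8. The normal approximation gives 2 × (1.960 + 0.842)² / 0.8² = 24.5, so 25 per group. The t-test solution is 25.52, so 26 (power 80.7%). Allowing for 10% loss, 26 / 0.9 = 28.9, so 29 per group and 58 in total. The stated figures reproduce. They concern the primary test only; the protocol gives no family-wise error figure.

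**Counting tests.** Assume one between-group test per measure per period.

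- Secondary, lowest count: 5 outcomes × 2 periods = 10.
- Secondary with four actimetry measures: (4 + 4) × 2 = 16.
- Reduced secondary plus exploratory set: 5 secondary outcomes, plus one performance, one fNIRS laterality and one EEG desynchronization measure for each of 3 tasks: (5 + 9) × 2 = 28.
- Broad set: 4 clinical, 4 actimetry, about 6 performance or kinematic, 36 fNIRS (3 summaries × 2 haemoglobin forms × 2 hemispheres × 3 tasks), 3 laterality and 12 desynchronization measures (2 bands × 2 hemispheres × 3 tasks) make 65 measures; × 2 = 130.

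**Independent tests, no true effect.** P(at least one p < 0.05) = 1 − 0.95^k.

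- k = 10: 1 − 0.5987 = 40.1%
- k = 13: 48.7%; k = 14: 51.2% (the point where one half is passed)
- k = 16: 1 − 0.4401 = 56.0%
- k = 28: 1 − 0.2378 = 76.2%
- k = 130: 99.9%

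**Correlated tests.** The protocol gives no correlations, so a range is shown. These are simulated z-tests with two contrasts per measure. A correlation of −0.5 is assumed between the two contrasts, because the periods share V2. A uniform correlation ρ is assumed between measures.

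| Tests | ρ = 0 | 0.3 | 0.5 | 0.7 | 0.8 |
|---|---|---|---|---|---|
| 10 | 38% | 35% | 31% | 26% | 22% |
| 16 | 53% | 48% | 41% | 32% | 27% |
| 28 | 74% | 66% | 55% | 41% | 33% |
| 130 | 99.8% | 98% | 88% | 66% | 51% |

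The ρ = 0 column differs slightly from the independence formula because the two contrasts of one measure remain correlated. If correlation is high only within a domain (0.5 to 0.8 within, 0.2 to 0.3 between), the 28-test set gives 55% to 66%. With 0.7 to 0.8 within and the same range between, the 130-test set gives 80% to 89%.

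**Expected count.** If every fNIRS, laterality and desynchronization cell were tested in both periods, (36 + 3 + 12) × 2 = 102 tests would give 102 × 0.05 = 5.1 expected false positives, whatever the correlation.

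**The case against.** The sentence can be read as the routine statement of a nominal level. It does not say that p-values will go unadjusted, and adjusted p-values judged against 0.05 would be compatible with it. The document also ranks its outcomes: one primary outcome carries the sample size, and the task, fNIRS and EEG measures are headed exploratory. These points have weight. They do not remove the difficulty, because the statistical sections never say that the rank changes what may be declared significant, and the rule is worded to reach every analysis.

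Four stronger readings are tempting, and the documents do not support them.

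- A reader might infer that the secondary outcomes alone would probably yield a false positive. The five named outcomes give 40% even under independence. Reaching 56% requires each actimetry measure to be a separate test, which no section states.
- A reader might take about five false biomarker findings as the plan's expected yield. That multiplies out every measurement cell. The exploratory analysis section names only the laterality index and desynchronization, as examples.
- A reader might infer that the Discussion plans a claim of benefit from secondary results alone. Its wording is conditional and joins primary with secondary results. The dissemination plan commits primary and secondary results to journal articles; the only exploratory reporting it specifies is baseline data in a thesis.
- A reader might infer that the confirmatory conclusion is compromised. The rule leaves the error rate of the primary test unchanged.

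**Conclusion.** The point stands as a badly fixed rule with moderate consequences. It permits unqualified significance claims on outcomes that the protocol itself ranks below the primary. With no true effect on any of them, the chance of at least one such false claim is about 40% for the 10 secondary tests and 56% for 16, under independence. Once exploratory measures are included it passes one half under most of the assumptions examined, but a small, highly correlated set stays below it (28 tests, ρ = 0.7: 41%). The test counts and correlations are assumptions, so these figures give the scale of the problem and do not predict what the trial will report. The sample size is unaffected.

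**What to change.** Reword the rule in the Statistical method section so that the 0.05 declaration applies only to the pre-specified primary WMFT comparison at V3. Name the score on which that comparison rests: the Primary outcome measure section lists four WMFT scores and gives important differences for both time and functional ability, so a single primary comparison is not yet fixed. Report secondary outcomes as between-group estimates with 95% confidence intervals and nominal p-values, labelled supportive. Report exploratory outcomes as hypothesis-generating.

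The change needs a short rewording plus a decision on the WMFT score. It does not require a choice between adjustment methods, more patients or different data collection. The cost is that the sponsor gives up unqualified significance claims on non-primary outcomes.

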The ReArm project is a randomized-control trial of late subacute and chronic stroke patients (> 3 months) designed to determine the impact of adding anodal HD-tDCS (2 mA, 20 min, ipsilesional motor cortex), compared to sham, during an intensive 3-week UL VRT program (13 × 30-min sessions) supplementing a conventional therapy program (39 × 30-min sessions). The primary objective will be to evaluate the impact of this intervention the on paretic UL function 3 months after the end of the rehabilitation. Secondary and exploratory objectives will be to investigate the evolution of the paretic UL use in ADL, performance, kinematics, and movement-related activation of motor cortical regions during functional motor tasks, from the beginning to the end of the 3-week program and after 3 months. We hypothesize that adding anodal HD-tDCS during VRT, as a supplement to conventional therapy rehabilitation program, will result in greater retention of clinical benefits 3 months after the intervention and increased use and functional recovery of the paretic UL.

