#### Other/exploratory outcome measures analysis

The outcome measures from the 3 functional motor tasks (Seated reaching, circular steering task, Armeo ladybug game) will be used to assess changes in UL performance (e.g., targets reached, IP, speed, accuracy, performance variability) and bihemispheric motor cortical regional activation (e.g., fNIRS-LI and EEG-ERD) from V1 to V2, and V2 to V3. Linear mixed models for the evolution of all these measures will be derived to assess the effect of time (V1, V2, V3) and of group (intervention, placebo). The interaction of group with time will be tested, along with the interaction of group with changes between V1 and V2 and between V2 and V3.

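### The secondary outcomes have no named between-group contrast at 3 months, and the V2–V3 change does not measure the benefit kept

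*Protocol article*

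**What the plan says.** Two sections fix the contrasts for the secondary outcomes. Statistical method: "The secondary outcomes will be the changes between V1 and V2 (learning) and between V2 and V3 (retention) for both groups". Secondary outcome measures analysis, for FM-UE, BBT, PANU, BI and actimetry: these "will be used to assess the changes in UL impairment, function, non-use, and ADL from V1 at inclusion to V2, and V2 to V3". Neither section mentions a V1–V3 change or a comparison of the arms at V3 for these five outcomes.

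The last paragraph of the Background states the hypothesis that adding stimulation "will result in greater retention of clinical benefits 3 months after the intervention".

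Three other statements bear on the point:

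- The primary analysis compares the arms at V3, on the WMFT only (Statistical method; Primary outcome measure analysis).
- Other/exploratory outcome measures analysis plans a model: "Linear mixed models for the evolution of all these measures will be derived to assess the effect of time (V1, V2, V3") and of group. It tests the overall group-by-time interaction and also the "interaction of group with changes between V1 and V2 and between V2 and V3".
- Descriptive analysis describes patients by arm at each visit, V3 included, but compares nothing.

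**The concern.** A claim of lasting benefit needs the difference between the arms at V3, given where they started. For the secondary outcomes the plan names two intervals that together span this period, but not the period itself.

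The interval labelled retention starts at V2, after treatment has already moved the outcome. Its between-group contrast therefore says how the treatment effect changed after V2. It does not say how much benefit remains. Read alone, it can suggest no retention where everything was kept, or poor retention in an arm that is still ahead. At stake is whether the five secondary outcomes give a direct, pre-specified 3-month estimate to set beside the WMFT result.

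**Working it through.** **The plan's own figure.** The Sample size section assumes a standardised effect of 0.8 on the WMFT at V3 and a 10% loss, and plans 58 recruits. It states: "Using an alpha bilateral risk of 5% and a power of 80%, 26 patients per group are needed for analysis". The normal approximation gives 2(1.960 + 0.842)² / 0.8² = 24.5, so 25 per arm. The two-sample t-test gives 25.52, so 26, with power 0.807 at 26. Then 26 / 0.9 = 28.9, so 29 per arm and 58 in total. The stated figures reproduce. I use 26 evaluable per arm below.

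**What each contrast estimates.** Let E2 and E3 be the between-group effects at V2 and V3. Randomisation makes the expected effect at V1 zero. Then:

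- V1–V2 contrast = E2
- V2–V3 contrast = E3 − E2
- V1–V3 contrast = E3 = sum of the two above

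Invented example: intervention +8 at V2 and +6 at V3 from baseline; sham +3 and +3. Then E2 = 5, E3 = 3, and V2–V3 = 3 − 5 = −2. The intervention arm is 3 points better at V3 and its retention contrast is negative.

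**Size.** The article gives no correlation between visits and no effect sizes for the secondary outcomes. I assume a common SD at each visit, an equal correlation ρ between visits (0.5, 0.7, 0.9) and E3 = 0.8 SD. The SD of a change is √(2(1 − ρ)) = 1.00, 0.77, 0.45, in units of the single-visit SD. The standard error of a contrast is that times √(2/26) = 0.277, 0.215, 0.124. Power is from the two-sample t-test.

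| Assumed pattern (SD) | Quantity | ρ = 0.5 | ρ = 0.7 | ρ = 0.9 |
|---|---|---|---|---|
| All patterns (E3 = 0.8) | Power, V1–V3 | 0.81 | 0.955 | >0.99 |
| +0.8, then 0 (fully kept) | Rejection rate, V2–V3 (true value 0) | 0.05 | 0.05 | 0.05 |
| +1.0, then −0.2 (partial decay) | P(V2–V3 estimate below 0) | 0.77 | 0.82 | 0.95 |
| +1.0, then −0.2 (partial decay) | P(V2–V3 significant against intervention) | 0.11 | 0.15 | 0.36 |
| +0.4, then +0.4 (gradual) | Power, each interval | 0.29 | 0.45 | 0.89 |

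The two probability rows use the normal approximation, e.g. Φ(0.2 / 0.277) = 0.77 at ρ = 0.5.

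**Why adding up two reported intervals is not enough.** Under equal correlation, each interval change has variance 2(1 − ρ) and their covariance is −(1 − ρ), so they correlate −0.5. The variance of the V1–V3 change is 2(1 − ρ) + 2(1 − ρ) − 2(1 − ρ) = 2(1 − ρ). A reader who adds the two published differences and treats them as independent gets 4(1 − ρ), a standard error √2 = 1.41 times too large. The point estimate can be recovered from two intervals; its precision cannot, unless it is reported.

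**The case against.** The best defence is the mixed model. It has V3 as a time level, a group effect and an overall group-by-time test, and V1–V3 is the sum of its two interval contrasts. If it covers the secondary outcomes, the 3-month effect is one line of output away. The WMFT is compared at V3 in any case. A reader might therefore infer from the two analysis sections that the 3-month effect is never estimated, or that the secondary outcomes cannot support the primary conclusion. The documents do not bear out either reading.

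Nor is the V2–V3 contrast defective. Compared between randomised arms, it validly estimates differential decay. In the example, −2 correctly says that the intervention arm lost more after V2. A reader might call that the wrong direction. It misleads only if read without the V1–V2 result or the V3 difference.

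A reader might also take the reference to both groups as a plan for within-arm tests. The wording is loose, but the model section does test group interactions, so this is not established.

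The missing SAP is a weaker defence, because the article itself states twice which contrasts define the secondary outcomes.

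What remains is this. The model stands under the exploratory heading, and its reference to the measures follows a sentence on the three functional motor tasks, so its reach to the secondary outcomes is unclear. If it does reach them, the overall interaction test has two degrees of freedom and no direction, and the specific contrasts named are again only the two intervals. If it does not, no 3-month between-group analysis is stated for these five outcomes.

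**Conclusion.** The point holds in a limited form. For FM-UE, BBT, PANU, BI and actimetry, the between-group effect at 3 months is not a named contrast, and the V2–V3 contrast alone does not measure the benefit kept. That follows from the text and from the identity V2–V3 = E3 − E2, without further assumptions.

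The sizes are illustrative and rest on the assumed effects, a common SD, equal correlations and 26 evaluable patients per arm. Over the range shown, a fully kept 0.8 SD benefit is seen by V1–V3 with power of at least 0.81 and by V2–V3 only at the 5% error rate. A benefit that builds evenly has power of 0.29 to 0.89 per interval. The WMFT analysis and the sample size are not affected. This is a worthwhile correction to the secondary analyses, not a threat to the trial's main result.

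**What to change.** 1. State that the group-by-time mixed model also applies to FM-UE, BBT, PANU, BI and actimetry.
2. For each of them, name the between-group difference at V3 adjusted for V1 as the main 3-month estimate, with its confidence interval.
3. Keep V1–V2 and V2–V3 as supporting contrasts, and say that both are differences between the arms.
4. State that V2–V3 describes the change in the treatment effect after V2 and is interpreted only alongside the V3 difference.

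Reducing V2–V3 to a purely descriptive summary would go further, but that is a matter of preference and is not needed.

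The cost is a few sentences and one extra contrast per outcome, from visits already scheduled and a model already described. No new data or patients are required.
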